## Abstract

**Objective:**

Acute kidney injury (AKI) is a common complication of complex aortic surgery with high mortality, morbidity and health care expense. The current definition of AKI does not allow for structural characterization of the kidneys and utilizes functional indices with substantial limitations leading to delayed diagnosis and ineffective interventions. The aim of this study is to develop a method of early detection of structural renal abnormalities that can precede and predict the occurrence of AKI in this population. We propose a novel combined index of ultrasonography (shear wave elastography), biomarkers of renal stress (urinary insulin growth factor binding protein-7, IGFBP-7 and inhibitor of tissue metalloproteinase-2, TIMP-2) and renal injury markers (urinary neutrophil gelatinase-associated lipocalin -NGAL)- the bio-sonographic index (BSI).

**Methods:**

A prospective observational study at a tertiary referral center will be performed enrolling 80 patients undergoing elective open and endovascular repair of the visceral aorta. The BSI will be evaluated at baseline, and at 6 and 24 hours after the procedure. The primary outcome is the occurrence of AKI according to the Kidney Disease Improving Global Outcomes (KDIGO) criteria. Each patient will be his/her own control. A reference group of 15 healthy volunteers who are not undergoing interventions will be enrolled to test the feasibility of and to refine the novel SWE protocol. The BSI will be tested for its predictability of the occurrence of AKI. Comparisons will be made between individual and combined components of the BSI and traditional markers used in the KDIGO definition; serum creatinine and urine output in terms of baseline status of the kidney. Correlations will be made between the BSI and conventional indices of AKI and exploratory analyses will be conducted to identify individual disease patterns using the BSI.

**Discussion:**

We hypothesize that the BSI will be a sensitive index of early structural abnormalities that precede and predict the occurrence of AKI as defined by KDIGO in complex vascular surgery.

**Trial registration:**

ClinicalTrials.gov NCT04144894. Registered 1/6/2020.

## Introduction

Postoperative acute kidney injury (pAKI) is a common complication of aortic aneurysm repair occurring in approximately 40% of patients [1–4]. Even in milder forms, pAKI has been associated with progression to chronic kidney disease (CKD), high mortality, morbidity and health care expense. Although patients may recover renal function after acute injury, there is no curative treatment available [5].

A major impediment to the provision of early and effective treatment for pAKI is the inherent delay in diagnosis due to limitations of available markers of kidney function, which are neither sensitive nor specific to the site, laterality, extent, etiology or reversibility of the injury [6–8]. Additionally, current novel biomarkers of renal injury such as neutrophil gelatinase-associated lipocalin (NGAL) suffer from the limitations of being non-specific to the etiology of renal injury, being heavily affected by preoperative kidney function status [9], lack of current consensus on cut off values [10], and the inability to use as therapeutic targets. As such, the diagnosis of pAKI continues to be delayed with consequential delay in initiation of effective and timely therapy and improved outcomes.

Whereas G1 cell cycle arrest (CCA) biomarkers (urinary insulin growth factor binding protein-7, IGFBP-7 and inhibitor of tissue metalloproteinase-2, TIMP-2) have been recently validated as markers of renal stress that predict the occurrence of pAKI [11, 12], they are affected by preoperative disease comorbidities, do not inform on non-tubular nephron pathology, and have been used in such a way that therapy based on their use has been confined to the postoperative period after the occurrence of the injury [13].

Shear wave elastography (SWE) has evolved as an ultrasound tool capable of measuring and quantifying tissue stiffness in response to stress. Tissue stress is applied by emitted U/S beam that generate shear waves, the velocity of propagation of which is measured as a surrogate of deformation (or elastance or stiffness) using Young’s Elastic Modulus (YM). The stiffer the tissue, the faster the propagation velocity [14]. Shear wave elastography has been recently used to assess renal tissue stiffness in patients with mild forms of chronic kidney disease (CKD) [15–17]. We hypothesize that detection of renal cortical stiffness may add to the diagnostic value of currently used renal biomarkers.

In this study, we propose a novel index that combines ultrasonography and biomarkers of renal stress and injury to early detect and predict the occurrence of AKI in patients undergoing complex vascular surgery.

## Methods

### Study design

This is a prospective observational study at a tertiary referral center. The study has been approved by the institutional review board of the University of Alabama at Birmingham. Fig 1 outlines the flow of the study.

**Fig 1 pone.0241782.g001:**

Proposal summary of the study. eGR: Estimated glomerular filtration rate, SWE; Shear wave elastography; uIGFBP-2/TIMP-7: urinary Insulin growth factor binding protein-7/tissue inhibitor of metalloproteinase-7; NGAL: neutrophil gelatinase-associated lipocalin; AAA: open Abdominal aortic aneurysm repair; TAA: Thoracoabdominal aneurysm repair; TEVAR: Thoracic endovascular aneurysm repair; PAKI: Postoperative acute kidney injury; KDIGO: Kidney Disease Improving Global Outcomes; EVAR: endovascular abdominal aneurysm repair, FEVAR: fenestrated endovascular abdominal aneurysm repair.

### Sample size calculation

Based on our prior experience and literature search of a 40% incidence of pAKI in this population encompassing both open and endovascular approaches of descending aortic aneurysm repairs [1, 18, 19], we expect 40% patients to develop pAKI and 60% of patients to not develop pAKI. We project that more than 70% of patients with a positive BSI to develop pAKI, while only 30% of those with a negative BSI to actually develop pAKI. From this assumption, if we recruit 80 patients to the study, we will have 32 patients expected to have pAKI (positive BSI) and 48 patients expected not to have pAKI (negative BSI). Using Fisher’s Exact Test with a 5% two-sided significance level, we will have minimum 90% power to detect the difference between 69% pAKI in patient group who will eventually develop pAKI (positive BSI) and 30% pAKI in patients who will not eventually develop pAKI (negative BSI), when sample sizes are 32 and 48, respectively. In addition, we will recruit 15 healthy group of participants to explore the feasibility of the SWE protocol, and to establish reference values on a sample of our population in terms of renal cortical stiffness, and renal parenchymal and vascular indices.

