### Procedures

The bio-sonographic index (BSI) will be performed on the study patients at baseline- during their preoperative visit, and at 6 hours and at 24 hours after the procedure. The BSI will be composed of SWE, urinary cell cycle arrest (uCCA) and urinary NGAL (uNGAL). Abnormal BSI will be diagnosed as an increase of at least 10% from baseline to any of the 6 and 24 hour time points. Based on an estimated incidence of pAKI of 40% in this population, a probability of abnormal BSI will be estimated as follows (Table 1).

**Table 1 pone.0241782.t001:** The BSI criteria.

AKI	combination	SWE (YM)	uCCA	uNGAL	Patients	AKI %
Y	Abnormal	≥10% = 1, < 10% = 0	≥10% = 1 < 10% = 0	≥10% = 1 < 10% = 0	40%	90%
N	Normal	SWE <10% = 0	< 10% = 0	< 10% = 0	60%	30%

* Values are in reference to a change from baseline to any of time points 2, and 3.

AKI (Y/N) = YM based on SWE & urine biomarkers

AKI: acute kidney injury; SWE: shear wave elastography; YM; Yong Elastic Module; uCCA: urinary cell cycle arrest; uNGAL, urinary neutrophil gelatinase-associated lipocalin; Y: yes; N: no; BSI: biosonographic index; BSI score is the sum of SWE, Biomarker, and NGAL. It is abnormal if ≥ 1. Total score can range from 0 to 3.

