### Statistical analyses

The analysis plan will include comprehensive graphical and statistical descriptions of the data. Baseline demographics, biomarkers, stratified by pAKI status will be summarized using descriptive summary statistics. Continuous variables will be summarized overall and within each group with the total numbers of observations, means with 95% confidence intervals, standard deviations and ranges. The two-sample t-test will be employed to compare the mean of continuous outcome variables while the Wilcoxon rank-sum test will be used for study outcomes that do not meet the normality assumption after performing appropriate data transformations. Categorical variables will be summarized overall and within each group with the total numbers of observations and percentages with exact 95% confidence intervals. To assess the accuracy and concordance of each marker with the pAKI status, we will calculate sensitivity and specificity. We will evaluate concordance (sensitivity and specificity) between pAKI status and SWE, uCCA, uNGAL alone and in combination. The BSI accuracy in predicting pAKI status will be evaluated in this study. To investigate the prognostic utility of bio-sonographic index for prediction of pAKI status, we will compare the sensitivity and specificity, using the 10% change from baseline to any of the 6 and 24 hour postoperative values alone as well as combined score (range: 0–3). Receiver operating curve (ROC) will be constructed for comparison between individual and combined components of SWE, uCCA, and uNGAL, and the differences in areas under the curve (AUC) will be assessed using a critical “z” ratio proposed by Hanley and McNeil. Intra-subject variability will be examined by comparing difference of individual readings from the median YM for each subject. The diagnostic performance of SWE and combination of each for distinguishing normal renal parenchyma from renal parenchyma affected by AKI will be assessed using a univariate logistic regression model to construct receiver operating characteristic (ROC) curves. ROC analyses will be performed to determine a cut-off point of SWE that would correctly classify the maximum number of participants based on sensitivity and specificity values. Wald asymptotic 95% confidence limits will be presented for sensitivity and specificity values. Percentile method 95% confidence intervals for ROC curves will be generated using the pROC package in R version 3.0.2 (Vienna, Austria) [28, 29]. Comparisons of area under the curves will be performed by use of a contrast matrix to take differences of the area under the empirical ROC curves. Pearson correlation coefficients will be used to assess the strength of association between continuous exposure variables. Stratified analysis of the control and AKI groups will be performed to evaluate for potential significant confounders of SWE values. SAS version 9.4 (Cary, NC) will be used for all other non-ROC related statistical analysis. Two-tailed p values of less than 0.05 will be deemed statistically significant.

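### The sample size calculation uses the expected pAKI split (32/48) as the BSI split, so its inputs contradict each other and do not determine the stated minimum 90% power

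*Protocol article*

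**What the plan says.** Under Sample size calculation, the protocol article starts from the outcome: "we expect 40% patients to develop pAKI and 60% of patients to not develop pAKI". It then projects outcome risk by index status: "We project that more than 70% of patients with a positive BSI to develop pAKI, while only 30% of those with a negative BSI". For 80 patients it derives the two groups to be compared: "we will have 32 patients expected to have pAKI (positive BSI) and 48 patients expected not to have pAKI (negative BSI". The power sentence names Fisher's exact test at a two-sided 5% level. It claims at least 90% power for 69% versus 30% pAKI with groups of 32 and 48, and describes those groups as the patients who will and who will not eventually develop pAKI.

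Under Procedures, the text before Table 1 makes the same link between incidence and index: "Based on an estimated incidence of pAKI of 40% in this population, a probability of abnormal BSI will be estimated". Table 1 has an abnormal row (40% of patients, 90% in the AKI column) and a normal row (60% of patients, 30% in the AKI column).

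No expected share of BSI-positive patients is stated separately from the pAKI incidence.

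**The concern.** Two different partitions of the 80 patients are treated as one. The 32/48 split follows from the incidence, so it divides patients by outcome. The 69% and 30% are outcome risks, which only make sense in groups divided by the index. Read literally, a group defined as going on to develop pAKI has 100% pAKI, not 69%, and the other group has 0%, not 30%.

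The two partitions coincide in size only if the BSI-positive share happens to equal the incidence. Once incidence and both risks are fixed, that share is no longer free, and the values given do not produce 40%.

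This paragraph is the only justification given for 80 patients. If its inputs cannot hold together, the power it quotes belongs to no scenario that the protocol as a whole describes.

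**Working it through.** **Inputs.** From Sample size calculation: N = 80; pAKI incidence 40%; pAKI risk above 70% (69% in the power sentence) if BSI positive and 30% if BSI negative; groups of 32 and 48; Fisher's exact test, two-sided 5%. From Table 1: 40%/60% of patients with 90%/30%. No loss of patients is assumed. Power is exact: the probabilities of all pairs of independent binomial counts with a two-sided Fisher p-value of at most 0.05 are summed.

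**1. The protocol's own figure.** 32 versus 48 at 69% versus 30% gives 92.8%. The claim of at least 90% is right for the numbers entered.

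**2. Consistency.** Let s be the BSI-positive share, p1 the pAKI risk if positive and p0 the risk if negative. Then incidence = s × p1 + (1 − s) × p0.

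- s = 0.40, 69%/30%: 0.40 × 0.69 + 0.60 × 0.30 = 0.276 + 0.180 = 45.6%.
- s = 0.40, 70%/30%: 0.280 + 0.180 = 46.0%.
- Table 1, if its 40%/60% is the BSI split: 0.40 × 0.90 + 0.60 × 0.30 = 54%.

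None of these is 40%.

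**3. Keep the 40% incidence and the projected risks.** Solving for the share, s = (0.40 − p0)/(p1 − p0).

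- 70%/30%: s = 0.10/0.40 = 25%, so 20 versus 60.
- 69%/30%: s = 0.10/0.39 = 25.6%, or 20.5 of 80, so 20/60 or 21/59.
- 75%/30%: s = 0.10/0.45 = 22.2%, or 17.8 of 80, so 18/62.

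**4. Keep 32/48 and the 40% incidence, and let one risk move.**

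- Hold 30% in negatives: p1 = (0.40 − 0.60 × 0.30)/0.40 = 55%.
- Hold 70% in positives: p0 = (0.40 − 0.40 × 0.70)/0.60 = 20%.

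**5. Exact power, N = 80.**

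| Groups (BSI+ / BSI−) | pAKI risks | Implied incidence | Power |
|---|---|---|---|
| 32/48 (as entered) | 69% vs 30% | 45.6% | 92.8% |
| 20/60 | 70% vs 30% | 40% | 85.6% |
| 20/60 | 69% vs 30% | about 40% | 83.5% |
| 21/59 | 69% vs 30% | about 40% | 87.1% |
| 18/62 | 75% vs 30% | about 40% | 91.2% |
| 32/48 | 55% vs 30% | 40% | 56% |
| 32/48 | 70% vs 20% | 40% | 99.5% |

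**6. The other conditioning.** Suppose 69% and 30% were meant as the proportions BSI positive among 32 pAKI and 48 non-pAKI patients. Then 32/48 is the right split and 92.8% stands. The implied pAKI risk would be 0.276/0.456 = 61% after a positive BSI and 0.124/0.544 = 23% after a negative one. That does not match the projected 70% and 30%.

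**The case against.** The strongest reply is that the power computation itself is correct and that the defect is one of labelling. That stands as far as it goes: 92.8% is right for what was entered, and a 32/48 BSI split with 69%/30% risks is possible. It simply belongs to a population with 45.6% pAKI.

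A reader might go further and infer that the study is underpowered, because 85.6% is below 90%. The documents do not support that as a general conclusion. The projection says more than 70%, which is a floor, and 75%/30% at 40% incidence gives 91.2%. The Introduction calls the incidence approximate, and at 42% with 70%/30% the split is (0.42 − 0.30)/0.40 = 30%, or 24/56, with 90.1% power. The shortfall belongs to the most literal reading, not to every consistent one.

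Table 1 is also ambiguous. Its rows are keyed by AKI yes/no, and its introduction speaks of the probability of an abnormal BSI. The 90%/30% could therefore be abnormal-BSI rates by outcome despite the column label, and then the 54% does not arise. The 54% is conditional on reading 40%/60% as the BSI split.

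A reader might also object that the Statistical analyses section does not list the powered Fisher test, that withdrawals are not allowed for, or that the precision of sensitivity and specificity is not given. A condensed article may leave these to a fuller document, and the article states no withdrawal rate, so they form no part of this point.

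Finally, the study calls itself exploratory and defers validation to a later trial. That lowers the stakes but does not make the paragraph consistent.

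**Conclusion.** The point holds as an internal contradiction in the sample size paragraph. The outcome split is used as the index split, the inputs imply 45.6% pAKI against a stated 40%, and the risk after a positive BSI is given as more than 70%, 69% and (on the natural reading of Table 1's column label) 90%.

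At 40% incidence with exactly 70%/30%, power is 85.6%, about 4 points under the stated minimum. With 69%/30% it is 83.5% to 87.1%, about 3 to 6.5 points under. Depending on which stated input gives way, consistent scenarios run from 56% to 99.5%. The supportable conclusion is that the stated assumptions do not determine the power, not that the trial is shown to fall short of 90%.

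These figures assume 80 evaluable patients, fixed group sizes and the two-sided Fisher test that the protocol names. The choice of test matters: the uncorrected normal approximation gives 90.1% at 20/60 with 70%/30%.

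**What to change.** Rewrite the paragraph on one conditioning, keeping 80 patients.

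- **By BSI status, as the text now projects.** State the expected BSI-positive share separately, make it agree with 40% incidence and the two pAKI risks, and restate the power. With 70%/30% that is a 25% share, 20/60 and about 86%. If a higher risk after a positive BSI is expected, state that value and the share that follows from it.
- **By pAKI status, only if that was the intention.** Say that 69% and 30% are the BSI-positive rates among 32 pAKI and 48 non-pAKI patients, and drop the 70%/30% risk projection. Power is then 92.8%. The authors should choose this only if they hold those rates as assumptions. The article states no such sensitivity or specificity, and they should not be adopted merely because they preserve the figure.

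In either case, reconcile 69%, 70% and Table 1's 90%, and label Table 1's columns so that it is clear which percentage is conditional on which status. The cost is wording in one paragraph and one table, with no extra patients. The downside is that the stated power may become slightly less favourable.

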### Participants

A total of 80 patients for the ‘study group’ will be enrolled. Each patient will serve as his/her own control by studying the change in BSI from preoperative values to 6 and 24 hr after the procedure. A total of 15 normal healthy volunteers will be enrolled as a ‘feasibility group’ to test the feasibility of the SWE protocol.

### Study patients

#### Inclusion criteria

Patients undergoing complex vascular surgery defined as open thoracoabdominal aortic aneurysm repairs (TAAA) and thoracic endovascular aneurysm repair (TEVAR), open abdominal aortic aneurysm repairs (AAA) and endovascular abdominal aneurysm repairs (EVAR), fenestrated endovascular abdominal aortic aneurysm repairs (FEVAR) and branched endovascular aortic aneurysm repairs (BEVAR).

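### The BSI is tested against AKI only by pooled, unadjusted methods across open and endovascular repair, so a positive result cannot show that it adds anything to knowing which operation was done

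*Protocol article*

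**What the plan says.** - **Cohort.** The Inclusion criteria list six procedures: open thoracoabdominal repair, TEVAR, "open abdominal aortic aneurysm repairs (AAA) and endovascular abdominal aneurysm repairs (EVAR"), FEVAR and BEVAR. The abstract describes the study as "enrolling 80 patients undergoing elective open and endovascular repair of the visceral aorta".
- **Sample size.** One AKI incidence of 40% serves the whole mix, "encompassing both open and endovascular approaches of descending aortic aneurysm repairs". Power is stated for one unstratified Fisher's "Exact Test with a 5% two-sided significance level", "when sample sizes are 32 and 48, respectively".
- **Index.** Under Procedures and Table 1, the BSI is abnormal if any one of SWE, uCCA and uNGAL rises by at least 10% from baseline at 6 or at 24 hours.
- **Analysis.** Statistical analyses plans sensitivity and specificity for each marker and for the combination, ROC comparisons, and a univariate logistic model for the ROC curves. None has a term or a stratum for procedure. The one sentence on confounding reads "Stratified analysis of the control and AKI groups will be performed to evaluate for potential significant confounders of SWE values".
- **Differences between procedures.** Table 2 (Perioperative procedures) lists clamping and unclamping for the two open columns only, and contrast agent for the two endovascular columns only. It has no FEVAR or BEVAR column.
- **Data.** Clamp sites and renal ischaemia time (Surgical technique, Open procedures), and clamp duration and contrast dose (Data collected), are recorded. They have no stated role in the BSI-AKI analysis.

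**The concern.** Type of operation is fixed before the first postoperative BSI is measured, and it may influence both sides of the comparison. One type may carry more AKI. The same type may also raise renal stiffness or the urinary markers more, whether or not the individual patient goes on to AKI. The BSI would then separate AKI from non-AKI patients in the pooled table partly by identifying who had the larger operation.

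Using each patient as his or her own control does not remove this. The operation falls between the baseline and the 6 and 24 hour measurements, so it acts on the change score itself.

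The article hopes for an index of early structural abnormality that precedes and predicts AKI, and intends to take it on to a randomised trial. For that purpose the useful question is what the BSI adds to information the clinician already has. The methods named do not address that question, whatever the result.

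**Working it through.** **1. The plan's own figure.** Inputs from Sample size calculation: 69% versus 30% AKI, groups of 32 and 48, two-sided 5% Fisher test, power of at least 90%. Exact enumeration gives 92.8%. The usual formula with continuity correction at 90% power and a 1:1.5 ratio gives 32 in the smaller group, hence 32 + 48 = 80. The stated power is reproduced, for one pooled table.

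**2. What procedure alone could produce.** Let s be the share of open (or larger) repairs, r the AKI rate and b the BSI-positive rate in each type (O, E), with BSI and AKI independent within each type. Then

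P(AKI | BSI+) = [s·b_O·r_O + (1−s)·b_E·r_E] / [s·b_O + (1−s)·b_E]

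P(AKI | BSI−) = [overall AKI − numerator above] / [1 − P(BSI+)]

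The documents give none of s, r_O, r_E, b_O or b_E. All are assumptions here.

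Worked example: s = 0.5, AKI 70%/10%, BSI-positive 90%/30%.
- P(AKI | BSI+) = (0.5×0.9×0.7 + 0.5×0.3×0.1)/(0.45 + 0.15) = 0.33/0.60 = 55%.
- P(AKI | BSI−) = (0.40 − 0.33)/0.40 = 17.5%.
- Sensitivity = 0.33/0.40 = 0.825. Specificity = 1 − 0.27/0.60 = 0.55. AUC of the binary index = (0.825 + 0.55)/2 = 0.69.
- Procedure alone: sensitivity 0.35/0.40 = 0.875, specificity 0.45/0.60 = 0.75, AUC = 0.81. Adding the BSI leaves this unchanged, because it carries no information within either type.

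**3. Range.** Simulated trials of 80 patients, pooled Fisher test against a Mantel-Haenszel test stratified by procedure:

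| Share open or larger | AKI, two types | BSI+, two types | Crude AKI, BSI+ vs BSI− | Pooled p<0.05 | Stratified p<0.05 |
|---|---|---|---|---|---|
| 40% | 75% / 25% | 90% / 10% | 68% vs 28% | about 93% | about 4% |
| 50% | 70% / 10% | 90% / 30% | 55% vs 17.5% | about 92% | about 4% |
| 50% | 70% / 20% | 80% / 20% | 60% vs 30% | about 75% | about 5% |
| 50% | 60% / 20% | 80% / 40% | 47% vs 30% | about 28% | about 5% |
| 50% | 55% / 25% | 70% / 30% | 46% vs 34% | about 16% | about 5% |
| 50% | 50% / 30% | 70% / 50% | 42% vs 37.5% | about 5% | about 5% |
| 50% | 70% / 10% | 95% / 80% | 43% vs 22% | about 17% | about 5% |
| 50% | 60% / 20% | 90% / 70% | 42.5% vs 30% | about 11% | about 5% |
| 50% | 50% / 30% | 90% / 70% | 41% vs 35% | about 5% | about 5% |

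**4. Which rows fit the BSI rule.** The rule is easy to meet. Suppose there is no true change and the within-patient percentage change has an SD of 10% to 20% (assumed). One look then exceeds 10% with probability 0.159 to 0.309. With three independent looks, 1 − 0.841³ = 40% to 1 − 0.691³ = 67% of patients would be positive; with six, 65% to 89%. The looks share a baseline and are not independent, so this is only a guide. It favours the rows with high positivity in both types, where inflation is smaller.

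**The case against.** - **Marginal accuracy is a legitimate target.** Sensitivity, specificity and AUC in the enrolled mix are valid quantities, and operative injury acting on the kidney is part of what the index is meant to detect. This stands. The pooled analyses are not wrong; they answer a different question from added value.
- **The large figures need strong assumptions.** To reproduce the hypothesised 69% versus 30% from procedure alone, AKI must be at least 69% in one type and at most 30% in the other, with the BSI tracking procedure closely. Low positivity after endovascular repair fits poorly with an any-of-three, either-time rule. This also stands. A reader might infer from the top rows of the table that a positive trial result would probably be spurious; without procedure-specific rates the documents do not support that.
- **A confounder check exists.** Looking at what shifts a marker within AKI and non-AKI groups is a recognised approach, and procedure could be one of the factors examined. But the sentence covers SWE values only, leaves out uCCA, uNGAL and the BSI, and does not name procedure.
- **Eligibility may be narrower than the list.** A reader might infer that any repair at any level is admitted. Perioperative procedures speaks of the visceral aorta and describes open AAA as juxta- or suprarenal. The looser EVAR and TEVAR wording is a minor point.
- **Exploratory study, SAP not shown.** The article calls itself exploratory, and added value could be left to the SAP or a later study. However, the article itself names the univariate method, so the point rests on what it states.
- **Stratified accuracy would be weak.** In the worked example the endovascular stratum has 40 × 0.1 = 4 AKI events and the open stratum 40 × 0.1 = 4 BSI-negative patients. This is a good reason not to replace the pooled analysis.

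**Conclusion.** The concern holds in a limited form. Statistical analyses relates the BSI to AKI without any account of procedure, in a cohort whose procedures differ, by the article's own Table 2, in features plausibly linked to AKI. A positive pooled result would describe accuracy in this mix. It would not show that the BSI informs beyond the type of operation.

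How much this matters numerically cannot be judged from the documents. With no association within procedure, and under assumed rates only, pooled significance runs from about 5% to over 90%, against 4% to 5% when stratified. High BSI positivity in both types, which the 10% rule makes plausible, keeps it between about 5% and 17% in the cases tried.

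Two stronger conclusions do not follow: that the prognostic objective goes unanswered altogether, and that the pooled comparison should lose its place as the main analysis.

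**What to change.** In Statistical analyses, keep the pooled Fisher and ROC analyses as planned and add the following.

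1. A prespecified supporting estimate of the BSI-AKI association adjusted for open versus endovascular repair, by Mantel-Haenszel or a logistic model with one procedure term.
2. The AUC of procedure type plus BSI compared with that of procedure type alone.
3. An extension of the confounder check from SWE to uCCA, uNGAL and the BSI, with procedure named as a factor.
4. Accuracy within each type of repair as description only.
5. A sentence limiting any claim of predictive value beyond procedure to what items 1 and 2 show.

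Separately, reconcile the EVAR and TEVAR wording in the Inclusion criteria with the visceral aorta described in the abstract and in Perioperative procedures.

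The cost is analysis wording; no new data are needed. With about 32 events (40% of 80) the adjusted estimates will be imprecise, and the stated power does not apply to them. Two strata also leave variation by aortic level within each, which should be acknowledged. If the SAP already contains an adjusted analysis, the article's text only needs to be aligned with it.
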